# Neoadjuvant plus adjuvant combined or sequenced vemurafenib, cobimetinib and atezolizumab in patients with high-risk, resectable BRAF-mutated and wild-type melanoma: NEO-TIM, a phase II randomized non-comparative study

**DOI:** 10.3389/fonc.2023.1107307

**Published:** 2023-02-09

**Keywords:** metastatic melanoma, cobimetinib, vemurafenib, atezolizumab, neoadjuvant therapy

## Abstract

**Background:**

Following the increased survival of patients with metastatic melanoma thanks to immunotherapy and targeted therapy, neoadjuvant approaches are being investigated to address the unmet needs of unresponsive and intolerant patients. We aim to investigate the efficacy of neoadjuvant plus adjuvant combined or sequenced vemurafenib, cobimetinib and atezolizumab in patients with high-risk, resectable *BRAF*-mutated and wild-type melanoma.

**Methods:**

The study is a phase II, open-label, randomized non-comparative trial in patients with stage IIIB/C/D surgically resectable, *BRAF*-mutated and wild-type melanoma, with three possible treatments: (1) vemurafenib 960 mg twice daily from day 1 to 42; (2) vemurafenib 720 mg twice daily from day 1 to 42; (3) cobimetinib 60 mg once daily from day 1 to 21 and from day 29 to 42; and (4) atezolizumab 840 mg for two cycles (day 22 and day 43).

Patients will be randomized to three different arms: A) *BRAF*-mutated patients will receive over 6 weeks (1) + (3); B) *BRAF*-mutated patients will receive over 6 weeks (2) + (3) + (4); C) *BRAF* wild-type patients will receive over 6 weeks (3) + (4). All patients will also receive atezolizumab 1200 mg every 3 weeks for 17 cycles after surgery and after a second screening period (up to 6 weeks).

**Discussion:**

Neoadjuvant therapy for regional metastases may improve operability and outcomes and facilitate the identification of biomarkers that can guide further lines of treatment. Patients with clinical stage III melanoma may especially benefit from neoadjuvant treatment, as the outcomes of surgery alone are very poor. It is expected that the combination of neoadjuvant and adjuvant treatment may reduce the incidence of relapse and improve survival.

**Clinical trial registration:**

eudract.ema.europa.eu/protocol.htm, identifier 2018-004841-17.

## Introduction

1

The survival of patients with stage IV melanoma has recently improved due to anti-PD-1 immunotherapies and BRAF/MEK combination targeted therapies, up to the recently reported 5-year overall survival (OS) rate of 52% with the combination ipilimumab/nivolumab (1–5). Almost 50% of patients with metastatic melanoma have the *BRAF*V600 mutation, with features of oncogene addiction to the *BRAF*-mutated gene (6). Translational data suggest that MEK and BRAF inhibition of oncogenic MAPK signaling can potentiate host antitumor immune response through its effects on T cells, including upregulation of melanoma antigen expression, upregulation of programmed death-ligand 1 (PD-L1) expression, and increased tumor T-cell infiltration (7–11). Combinations of MEK inhibitors with anti-PD-1/PD-L1 therapy have demonstrated synergistic tumor growth inhibition and reactivation of antitumor immunity in murine models (12). Moreover, early-phase clinical studies have demonstrated promising antitumor activity and restoration of antitumor immunity with combinations of MEK inhibitors and anti-PD-L1 antibodies in patients with BRAFV600 wild-type advanced melanoma (13).

In a phase I study (NCT01988896), the combination of cobimetinib, a MEK inhibitor, with atezolizumab, an anti-PD-L1 antibody, had promising anti-tumor activity. Indeed, the CD8 + T-cell infiltration and the MHC I expression in tumor tissue increased after starting the cobimetinib run-in and adding atezolizumab to cobimetinib compared to baseline (14). Contrary to these results, the phase III trial Imspire170, which compared pembrolizumab alone with atezolizumab and cobimetinib combination in patients with *BRAF*V600 wild-type (WT) advanced melanoma, did not meet the primary endpoint (15). This study showed a higher benefit with the combination than with anti-PD-1 alone in the first 4 months, suggesting the use of short-course MEK inhibitor + anti-PD-1/PD-L1 in a neoadjuvant setting (15, 16).

In addition, treatment with atezolizumab and vemurafenib (a BRAF serine–threonine kinase inhibitor) with or without cobimetinib had higher response rates and faster and longer-lasting responses than cobimetinib plus vemurafenib or atezolizumab alone in previously untreated *BRAF*V600 mutation-positive advanced melanoma (17). The ongoing IMspire 150 phase III trial compares the combination cobimetinib-vemurafenib to either atezolizumab or placebo in *BRAF*v600 mutation-positive unresectable or advanced melanoma (18). At a median follow-up of 18.9 months (IQR: 10.4–23.8), the investigator-assessed progression-free survival was significantly longer with atezolizumab compared with placebo (15.1 vs 10.6 months; hazard ratio [HR]: 0.78; 95% CI: 0.63–0.97; p=0.025). Moreover, the median duration of response was longer in the atezolizumab group (21.0 months; 95% CI: 15.1–not estimable) than in the control group (12.6 months; 95% CI: 10.5–16.6), while safety was comparable in the two groups (18).

To address unmet needs for unresponsive and intolerant patients, neoadjuvant approaches arebeing investigated. This approach could provide blood and tumor tissue samples, obtained before and after the systemic therapy, for biomarker assessment and better treatment individualization Moreover, neoadjuvant treatment may avoid extensive unnecessary surgery increasing HRQOL (19), and could increase the proportion of RO resections (20).

It has recently been demonstrated that treatment with neoadjuvant and adjuvant targeted therapy with dabrafenib and trametinib is associated with a high pathologic complete response (pCR) rate and improved outcomes over surgery alone (21). Also, treatment with immune checkpoint blockade (ICB) studied in the neoadjuvant setting has provided very high pathologic rates and low recurrence rates in responding patients. Moreover, preclinical studies suggest that neoadjuvant administration of ICB is associated with improved survival and enhanced and long-lasting anti-tumor immune response compared with the same therapy administered in the adjuvant setting (22).

Prospective neoadjuvant clinical trials with targeted (dabrafenib/trametinib combination) or immunotherapeutic agents (nivolumab alone or nivolumab/ipilimumab combination) are ongoing in high-risk melanoma patients with overall promising preliminary results (20, 21, 23). In a pooled analysis of six clinical trials of anti-PD-1-based immunotherapy or BRAF/MEK-targeted therapy, a pCR occurred in 47% of patients with targeted therapy and 33% with immunotherapy (43% combination and 20% monotherapy). Accordingly, pCR correlated with improved recurrence-free survival (2-year pCR 89% versus no pCR 50%, p<0.001) and OS (2-year pCR OS 95% versus no pCR 83%, p=0.027) (24).

Based on current evidence, we planned to investigate neoadjuvant with adjuvant treatment with targeted therapy and immunotherapy in combination or sequence recording anti-tumor activity risk and site of relapse after surgery, safety, and correlation between clinical and pathologic responses in high-risk surgically resectable, melanoma (stage III B/C/D).

## Methods and analysis

2

### Study design

2.1

NEO-TIM is a phase II, open-label, randomized non-comparative trial with neoadjuvant plus adjuvant therapy in combination or sequence, of targeted therapy and immunotherapy, in patients with stage IIIB/C/D surgically resectable, *BRAF*-mutated and WT melanoma. The study design is presented in **Figure 1**.

**Figure 1 f1:**
[figure not shown]
Study design.

### Selection of subjects

2.2

The study will enroll 88 subjects with surgically resectable *BRAF*-mutated and *BRAF* WT cutaneous melanoma. The detailed inclusion and exclusion criteria are summarized in **Table 1**.

Table 1Eligibility criteria for NEOTIM.

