**Table d95e540:** 

Key inclusion criteria
•Patients of either sex aged ≥18 years Q11 •Capable of giving written informed consent, which includes compliance with the requirements and restrictions listed in the consent form •Patients must have histologically or cytologically confirmed stage IIIB/C/D 1 resectable cutaneous melanoma O The definition of resectability can be determined by the patient’s surgical oncologist and verified via discussion at the team of the Multidisciplinary Tumor Conference attended by melanoma medical and surgical oncology staff. Resectable tumors have no significant vascular, neural, or bony involvement. Only cases where a complete surgical resection with tumor-free margins can safely be achieved are defined as resectable •All patients must have a BRAF V600E/K mutation status known •Patients must be medically fit enough to undergo surgery as determined by the surgical oncology team •Patients must have measurable disease, defined by RECIST 1.1 •ECOG performance status 0–1 •Patients must have adequate organ and marrow function

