### Sample size

2.5

This study is designed as a phase II randomized, non-comparative trial, with pCR as the primary endpoint. According to Amaria et al. (21), a 60% pCR rate may be assumed in arms A and B. A sample size of 27 patients in each arm is sufficient to give at least a 90% probability of rejecting a 30% pCR rate with an exact 5% one-sided significance test when the true pCR rate is 60%. The null hypothesis of a pCR of 30% will be rejected if a pCR is observed in at least 12 patients.

According to Huang et al. (25), a pCR rate of about 30% may be assumed in arm C. A sample size of 34 patients is sufficient to give an 80% probability of rejecting a pCR rate of 15% with an exact 5% one-sided significance test when the true pCR rate is 35%. The null hypothesis of a pCR of 10% will be rejected if a pCR is observed in at least 10 patients.

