### Data analysis

2.6

All enrolled patients receiving at least one dose of the study medication will be considered the intention-to-treat population (ITT). The patient subgroup of the ITT population receiving at least one dose of the study drug will define the safety population. The analysis of efficacy endpoints will be performed in the ITT population, whereas the safety analysis will be performed in the safety population. A primary data analysis assessing the primary endpoint will be available after the neoadjuvant phase. A final data analysis will be available at study closure. The safety analysis will be completed within 12 months from the last visit of the last patient.

Primary endpoint results will be reported as counts and rates with confidence intervals. No comparisons among arms are planned. Demographical and clinical characteristics will be presented as descriptive statistics and summarized according to the treatment arm. Categorical variables will be given as counts and percentages, quantitative ones as mean and standard deviation, or median and interquartile range, as appropriate. No adjustment for multiple testing will be made.

Safety and tolerability will be assessed regarding AEs, laboratory data, ECG data, vital signs, and weight, which will be collected for all patients. AEs [both in terms of MedDRA preferred terms (26) and CTCAE 5.0 grade (27)], laboratory data, ECG data, vital signs data, and weight will be listed individually by the patient and summarized. Prevalence of related AEs, by grade, will be presented with a 95% CI. Survival will be represented with Kaplan-Meier curves, from which the median with 95% CIs will be derived.

Due to the small sample size, statistical analysis of biomarkers data will be conducted with the aim of hypothesis generation. A complete description of the data will be done. For biomarkers that might change over time due to treatment, levels before and after treatment will be compared with appropriate statistical tests based on the data type. Correlation with outcomes will be evaluated with univariate regression models. p ≤ 0.05 will be considered significant, and no adjustment is planned for multiple comparisons due to the exploratory nature of the analysis.

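### Three single-stage arms enrol patients whose disease is already resectable with no futility look on pCR; one non-binding look per arm would cost at most about 0.4 points of power

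*Protocol article*

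**What the plan says.** Section 2.2 fixes total enrolment across both mutation groups: "The study will enroll 88 subjects with surgically resectable" tumours. For the meaning of resectability, Table 1 has this: "Only cases where a complete surgical resection with tumor-free margins can safely be achieved are defined as resectable".

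Section 2.5 describes each arm by one sample size and one rejection count. Arms A and B have 27 patients apiece, meant to deliver 90% power or more against a 30% null if the truth is 60%, at a one-sided exact level of 5%. Their decision rule reads: "The null hypothesis of a pCR of 30% will be rejected if a pCR is observed in at least 12 patients". Arm C has 34 patients, a 15% null, 80% power at 35%, and rejection at 10 or more pCRs. The sentence giving that count names a 10% null instead.

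Section 2.6 names two efficacy analyses. The first is described as follows: "A primary data analysis assessing the primary endpoint will be available after the neoadjuvant phase". The other comes when the trial closes. No second stage, interim look or accrual hold is described for any arm.

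**The concern.** pCR is read from the surgical specimen soon after a 6-week course, in an open-label trial that names one recruiting centre and plans no comparison between arms. Results therefore accumulate while an arm is still enrolling, and looking at them would break no blind.

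By the entry criteria, each patient could have a complete resection at the outset and postpones it for the neoadjuvant course. If an arm's true pCR rate is at or below the rate the trial regards as uninteresting, the design as described still fills all 27 or 34 places. What is at stake is how many patients take on that delay and drug exposure after the data could already have argued against continuing, and whether the single-stage form gains enough power to justify it.

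**Working it through.** **Inputs (Sections 2.2 and 2.5).** Arms A and B: n = 27 each, null 30%, alternative 60%, printed cut-off 12. Arm C: n = 34, null 15% (10% also printed), alternative 35%, cut-off 10. Total: 27 + 27 + 34 = 88, as stated.

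**Step 1: reproduce the stated design (exact binomial).**

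| Rule | Type I error | Power |
|---|---|---|
| A/B, at least 12 of 27 (printed) | 7.98% at 30% | 96.6% at 60% |
| A/B, at least 13 of 27 | 3.59% at 30% | 92.6% at 60% |
| C, at least 10 of 34 | 2.40% at 15% | 80.4% at 35% |

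The 80% for arm C reproduces. For A/B, at least 90% power within a 5% level holds at n = 27 only with cut-off 13; the printed 12 exceeds the level. That is a separate error, but it decides which power figure goes with the look.

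**Step 2: add one look, keeping n and the final cut-off.** Let X1 be the pCRs among the first n1 patients and X2 those among the rest. Hold accrual if X1 ≤ a; otherwise continue to n and reject if X1 + X2 ≥ r.

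- P(hold) = P(X1 ≤ a)
- P(reject) = sum over x > a of P(X1 = x) × P(X2 ≥ r − x)

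The looks are n1 = 15, a = 4 in A and in B, and n1 = 18, a = 2 in C.

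| Arm, cut-off | Power without look | Power with look | Type I error without → with |
|---|---|---|---|
| A/B, 12 | 96.63% | 96.27% | 7.98% → 7.74% |
| A/B, 13 | 92.57% | 92.39% | 3.59% → 3.55% |
| C, 10 (null 15%) | 80.45% | 80.12% | 2.40% → 2.37% |

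A futility-only look removes rejection paths and adds none, so it cannot raise the type I error. That remains true if the sponsor overrides it.

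**Step 3: how often the look closes an arm.**

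| True pCR rate | A/B (≤4 of 15) | C (≤2 of 18) |
|---|---|---|
| 5% | – | 94.2% |
| 10% | 98.7% | 73.4% |
| 15% (null, C) | – | 48.0% |
| 30% (null, A/B) | 51.5% | 6.0% |
| 35% (alternative, C) | – | 2.4% |
| 60% (alternative, A/B) | 0.9% | – |

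**Step 4: patients saved per arm at the null.** Saving = P(hold) × (n − n1 − overrun), where overrun is the number entering while pCR is awaited. The article gives no accrual rate, so overrun is an assumption.

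| Overrun | A or B: 0.5155 × (12 − overrun) | C: 0.4797 × (16 − overrun) |
|---|---|---|
| 0 | 6.2 | 7.7 |
| 2 | 5.2 | 6.7 |
| 6 | 3.1 | 4.8 |
| 9 | 1.5 | 3.4 |
| 12 | 0 | 1.9 |

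**Step 5: sensitivity of arm C.** Section 2.5 also speaks of an expected rate of about 30%. Power there is 59.4% without the look and 59.0% with it, so the shortfall comes from the stated design. Placement matters: 2 or fewer of 17 would give 79.8%, just under the stated 80%.

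**The case against.** A single-stage exact test is a valid phase II design, and nothing in these passages is false on this point. The article is also a condensation, and the full protocol, which is not shown, could hold an accrual rule. That caveat stands. However, a two-stage rule would appear in the sample-size statement itself, so reading Sections 2.5 and 2.6 as single-stage is fair.

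A reader might infer that the look closes an inactive arm about half the time. It does not: half is the closing chance at the null rates. The Introduction reports pooled pCR rates of 33% with immunotherapy and 20% with monotherapy, so a 30% arm is insufficiently active rather than inactive. For nearly inactive arms the closing chance is far higher, as the 5% and 10% rows show.

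A reader might also take the Introduction's report that the phase III trial of the arm C pair "did not meet the primary endpoint" as evidence that arm C is inactive. The document does not support that. The comparator was an active drug, the disease was advanced, and the same paragraph uses the benefit in the first 4 months to argue for short neoadjuvant use.

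Three costs are real. Closing A or B ends randomization among BRAF-mutated patients, so the plan must say what follows; as no between-arm comparison is planned, no test is lost. A held arm gives fewer patients for recurrence-free survival, overall survival and biomarkers. A rule based on pCR alone also ignores partial responses, whose value the Discussion treats as unsettled. Making the look non-binding limits the last two. Finally, the saving shrinks with overrun and disappears in A/B at 12.

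**Conclusion.** The point holds as a cheap improvement, not as an error that invalidates the design. Sections 2.2, 2.5 and 2.6 describe three single-stage arms with no futility look, in patients who could have surgery at entry. One look per arm costs 0.2 to 0.4 percentage points of power and leaves the stated 90% and 80% intact, whether the A/B cut-off is 12 or 13.

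The conclusion rests on the printed sample sizes, on pCR being available while an arm is still recruiting, and on no further rule in the full protocol. The size of the saving depends on an overrun that the article gives no means of estimating. The arm C closing chance depends on which of its two printed nulls is meant.

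**What to change.** Add to Sections 2.5 and 2.6 one non-binding futility look on pCR per arm, affecting accrual only:

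- **Arms A and B:** after the first 15 patients in each, hold further enrolment in that arm at 4 or fewer pCRs.
- **Arm C:** after the first 18 patients, hold further enrolment at 2 or fewer pCRs.
- **Unchanged:** the sample sizes and final tests, apart from the corrections below. Patients already enrolled continue as planned.
- **If A or B is held:** state that new BRAF-mutated patients fill only the remaining places of the open arm.
- **Power statement:** match it to the cut-off. For A/B it is 96.3% with 12 of 27, whose type I error of about 8% needs separate correction, or 92.4% with 13 of 27. For C it is 80.1% at 35% with 10 of 34, once the 15% and 10% nulls have been reconciled.
- **Accrual during the look:** say whether enrolment pauses while pCR is read or how many further entrants are accepted.

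The cost is a short amendment and one tabulation per arm of data already collected, plus the small power loss, a thinner secondary data set in any held arm, and either a brief pause or some overrun. If the sponsor prefers to keep a single stage, one sentence in Section 2.5 giving the reason would answer the point.

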**Table d95e540:** 

Key inclusion criteria
•Patients of either sex aged ≥18 years Q11 •Capable of giving written informed consent, which includes compliance with the requirements and restrictions listed in the consent form •Patients must have histologically or cytologically confirmed stage IIIB/C/D 1 resectable cutaneous melanoma O The definition of resectability can be determined by the patient’s surgical oncologist and verified via discussion at the team of the Multidisciplinary Tumor Conference attended by melanoma medical and surgical oncology staff. Resectable tumors have no significant vascular, neural, or bony involvement. Only cases where a complete surgical resection with tumor-free margins can safely be achieved are defined as resectable •All patients must have a BRAF V600E/K mutation status known •Patients must be medically fit enough to undergo surgery as determined by the surgical oncology team •Patients must have measurable disease, defined by RECIST 1.1 •ECOG performance status 0–1 •Patients must have adequate organ and marrow function

**Table d95e567:** 

Key exclusion criteria
•No previous cancer therapy (chemotherapy, radiation therapy, immunotherapy, or biologic therapy) •Prior malignancy except for the following: adequately treated basal cell or squamous cell skin cancer, in situ cervical cancer, thyroid cancer (except anaplastic), or any cancer from which the patient has been disease-free for 2 years •Any major surgery within the last 3 weeks •Uncontrolled diabetes, hypertension, or other medical conditions that may interfere with the assessment of toxicity •Current use of anticoagulants (warfarin, heparin, direct thrombin inhibitors) at therapeutic levels •History of uncontrolled cardiovascular or interstitial lung disease and evidence or risk of retinal vein occlusion or central serous retinopathy •Subjects with conditions requiring systemic treatment with corticosteroids (>10 mg daily prednisone equivalents) or other immunosuppressive medications within 14 days of treatment. •Prior BRAF- or MEK-targeted therapy; patients who have received prior interferon are eligible •History of retinopathy or any finding at the ophthalmologic examination that is considered a risk factor for neurosensory retinal detachment/central serous chorioretinopathy, retinal vein occlusion, or neovascular macular degeneration •Prior BRAF- or MEK-targeted therapy; patients who have received prior interferon are eligible. •History of ocular/uveal/mucosal melanoma •Presence of any of the following risk factors for retinal vein occlusion: O Uncontrolled glaucoma with intra-ocular pressures ≥21 mmHg O Serum cholesterol grade ≥2; O Hypertriglyceridemia grade ≥2 O Hyperglycemia (fasting) grade ≥2 •Correct QT interval >450 ms to baseline, history of congenital long QT syndrome •Uncontrolled medical conditions, among which endocrine disorders (such as hypothyroidism, hyperthyroidism, and diabetes) •Other severe medical or psychiatric conditions (e.g., depression) or abnormalities of laboratory tests that may increase the risk associated with study participation or the assumption of vemurafenib, atezolizumab, and cobimetinib or that may interfere with the interpretation of study results, which in the judgment of the Investigator can make the patient not eligible for the study •Uncontrolled intercurrent illness, including but not limited to: ongoing or active infection, symptomatic congestive heart failure, uncontrolled hypertension, unstable angina pectoris, cardiac arrhythmia, cerebrovascular accident or transient ischemic attack, pulmonary embolism, interstitial lung disease, chronic gastrointestinal serious conditions associated with diarrhea or psychiatric illness/social situations that would limit compliance with study requirement, substantially increase risk of incurring adverse events or compromise the ability of the patient to give written informed consent •History of active primary immunodeficiency •Receipt of live attenuated vaccine within 30 days before the first dose. Note: enrolled patients should not receive a live vaccine while receiving study treatments and up to 30 days after the last dose of study treatment •Prior treatment with an anti-PD-1, anti-PD-L1, anti-PD-L2, or anti-CTLA-4 antibody •Known allergy or hypersensitivity to any of the study drugs or any of the study drug excipients •Positive test for HBV sAg or hepatitis C virus ribonucleic acid (hepatitis C virus antibody) indicating acute or chronic infection •Known history of testing positive for HIV or known AIDS •Judgment by the investigator that the patient is unsuitable to participate in the study and the patient is unlikely to comply with study procedures, restrictions, and requirements.
